
### Definition of disease flare

We defined a psoriasis flare as a PASI score > 5. A short disease flare was defined as a flare at one time point, and a persistent flare as a PASI > 5 for at least 3 months. Successful DR was defined as use of a lower biologic dose and a PASI ≤ 5. A PASI cutoff of 5 was chosen in absence of a validated definition for psoriasis flare. This cutoff was based on our previous DR trial [31], where PASI 5 was chosen based on expert opinion and on previous data that showed that patients who remain on a biologic reach average PASI scores ≤ 5 [32]. Although disease flare is based on disease activity only, quality of life measured by DLQI is incorporated in the tightly controlled DR strategy. In patients where PASI 5 reflects active disease, patients can always return to their previous effective dose or the normal dose when they experience larger impact of their psoriasis on their quality of life. Incidence of persistent flares was chosen as primary outcome to assess non-inferiority. Brief, temporary flares that improve after treatment adjustments or reintroduction of higher doses, and without large impact on overall disease control, might occur more frequent in a DR arm and are inherent to such a strategy. However, to not harm the patient, such effects should not last too long. For this reason, persistent flares are chosen as the primary outcome. PASI is used instead of Psoriasis Global Assessment (PGA) as PASI is a common used tool in Europe daily practice and in clinical trials. Assessment of PASI is standardized, whereas for PGA different scales and subtypes are used [33]. PASI has been reported to be a reliable instrument to evaluate treatment success when measured at baseline and during treatment [34].

### Power and sample size analyses

The primary outcome is non-inferiority of persistent flares (PASI > 5 for ≥ 3 months) in the intervention group with a non-inferiority margin of 15%. If the upper limit of the 95% confidence interval of the difference in persistent flares between the intervention group versus control group exceeds 15% at 18 months of follow-up, it must be concluded that non-inferiority could not be demonstrated for DR [36]. A margin of 15% was chosen based on clinical grounds, and on previous DR studies [8, 37]. Inherent to the intervention, there could be a small increase in disease flares (i.e., loss of disease control) as drug dosages are lowered. However, it is expected, based on other studies [8, 35], that most flares will be easy to control in the end without residual damage for patients, for example by reintroduction of a higher dose or switch to another biologic. It is therefore expected that persistent flares will not occur very frequently, as has also been shown in the CONDOR trial [8]. In addition, in the UC arm, there will be disease flares as well, as PASI scores might fluctuate over time and some patients might experience loss of effectiveness of their biologic [38]. The chosen non-inferiority margin of 15% is to some extent arbitrary, but refers to a clinically acceptable difference in persistent flares. Of note, the point estimate should be much lower than the margin of 15%, because the margin refers to the upper limit of the 95% confidence interval of the difference in persistent flares which should not exceed 15%. Therefore, we found a margin of 15% (hence a point estimate << 15%) for the difference in persistent flares acceptable, especially because we know that effectiveness could often be regained in patients with persistent flares in studies on other biologics [8, 35]. With an expected chance of being able to reduce biologic dosages in > 50% of patients [8], the benefit-harm ratio seems well balanced by accepting this anticipated increase of persistent flares in patients undergoing DR compared to UC.

With this margin, one-sided testing (*α* = 0.025; 1 − β = 0.8) and a randomization ratio of 2:1 DR versus UC, we calculated that 222 patients need to be included to reject the null-hypothesis of inferiority. Taking a drop-out rate of 10% into account, 244 patients need to be included, with 162 in the DR arm and 82 in the UC arm.

### Data collection and management

All data will be collected and entered in Castor, an electronic data management system, which is setup for clinical trials [39]. Data will be coded and kept based on the rules for good clinical practice (GCP) by GCP-certified personnel [40]. Handling of personal data will comply with the General Data Protection Regulation [41]. All blood samples will be coded before sending to Ghent University Hospital for storage and to University Hospitals Leuven where the samples will be analyzed.

### Statistical analyses

All analysis will be done according to a per protocol analysis, as this is the preferred and most conservative analysis for non-inferiority studies [42]. Of note, all patients that follow the DR protocol (Fig. 1) will remain in the group they were allocated to, including DR patients that returned to their normal dose according to the protocol. Patients on a lower dose who should return to a higher dose according to the protocol are not included in per protocol analysis after the moment of protocol deviation. They will however complete the study procedures, and occurred protocol deviations will be summarized and reported. Subjects lost to follow-up will be included in analyses until their lost to follow-up date only. Information about patients lost to follow-up will be described. Intention-to-treat (ITT) analysis will be performed as well on all outcomes for sensitivity reasons, and as they are needed for the cost-effectiveness analysis. Data of patients who deviated from the protocol will be included in ITT analysis. For the ITT analyses, last observation carried forward (LOCF) will be used for imputation of missing data. The last available data from patients who are lost to follow-up will be imputed. Extent and nature of missing data will be described. Patient and treatment characteristics will be summarized as means or medians and percentages, depending on the type of measurement.

The primary outcome incidence proportion of persistent flares will be calculated for both groups. Number of patients with a persistent flare will be presented as proportions with corresponding confidence intervals. Confidence intervals of proportions will be calculated by Fishers exact tests (Clopper-Pearson), and the proportions will be compared using Fisher exact tests (open source calculator OpenEpi, V3.01) [43]. If the difference in incidence proportion of persistent flares in the intervention group versus the UC group exceeds the non-inferiority margin (15% difference in persistent flares) at 18 months of follow-up, it will be concluded that non-inferiority could not be demonstrated for DR. Time until the first persistent flare in both groups will be graphically presented by Kaplan-Meier survival estimation.

The proportion of patients with successful DR will be expressed using descriptive statistics. PASI and DLQI course throughout the study will be compared between the intervention and control groups using mixed methods analysis. All disease-activity scores (PASI) will also be directly compared at each time point (every 3 months) between the two groups using an unpaired *t* test or a non-parametric alternative. PASI and DLQI at 12 and 18 months will be analyzed with ANCOVA in which the baseline values will be included as a covariate to gain efficiency. A multivariable regression analysis will be carried out in order to identify predictors for successful DR at month 12 and month 18. Possible candidate predictors will include baseline patient and treatment characteristics and baseline trough drug concentrations. Based on group size, we will test the four most promising variables. Proportions, rate ratios, and relative rate ratios, with corresponding confidence intervals, of SAEs and AEoSI will be described and differences between groups will be tested using classical statistical methods (Fisher exact test). SAEs and AEoSI *related to* DR will also be counted and expressed as proportions and rate ratios. A subanalysis for all outcomes will be made for the different drug classes and on individual drug level if appropriate (depending on numbers included per class).

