### Dose reduction group

The doses of secukinumab, ixekizumab, brodalumab, guselkumab, risankizumab, or tildrakizumab will be lowered by interval prolongation in two steps to 66% and 50% of the original dose, respectively (Table 1). The intervals of drug administration will be prolonged depending on the PASI and DLQI score (Fig. 1). DR is allowed in case of low disease activity, defined as PASI ≤ 5 and DLQI ≤ 5. First, the dose will be decreased to 66% of the normal dose of the biologic (by interval prolongation with a factor 1.5). After 3 months, if there remains low disease activity (PASI ≤ 5 and DLQI ≤ 5), the dose will be further reduced to 50% of the original dose (by doubling the original interval). When disease flare occurs (PASI > 5 and/or DLQI > 10), or when the patient is not willing to further use the lower dose, the patient will return to the previous effective dosing interval. In case of PASI ≤ 5 and DLQI > 5 but ≤ 10, it will be discussed with the patient if the reduced dose remains acceptable and can be continued or not. If possible, the patient will stay on the lowest dose. Each step will be analyzed after 3 months, or when the patient visits earlier due to complaints. In case a patient returned to the previous effective dosing interval, the dose will not be reduced again at a later time point. Topical therapies and concomitant use of methotrexate or acitretin are allowed. When there is still no disease control after reintroduction of the normal dose, treatment will be adjusted. Topical and/or systemic therapy will be optimized and, when required, the dose of the biologic will be increased or patients will switch to another agent. In case of treatment alternations, the patient will remain in the study for follow-up.

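### The main per protocol analysis stops including dose-reduction patients who flare but stay on the lower dose, generally before the flare can count as persistent, and this can bias the result toward non-inferiority

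*Protocol article*

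**What the plan says.** **Endpoint.** Under Definition of disease flare, the primary event is "a persistent flare as a PASI > 5 for at least 3 months". The Power and sample size section sets a margin of 15 percentage points, judged on the upper 95% limit of the difference at 18 months.

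**Step-back rule, DR arm.** The Dose reduction group section sets the trigger: "When disease flare occurs (PASI > 5 and/or DLQI > 10), or when the patient is not willing to further use the lower dose". Such a patient then goes back to the last interval that worked.

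**Analysis set.** The Statistical analyses section says: "All analysis will be done according to a per protocol analysis, as this is the preferred and most conservative analysis for non-inferiority studies". DR patients who step back as required stay in their arm. Patients on reduced dosing "who should return to a higher dose according to the protocol are not included in per protocol analysis after the moment of protocol deviation". These deviators still finish the study procedures. ITT is planned for every outcome, includes deviators, and is described as a sensitivity analysis.

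**UC arm.** The Control group section leaves flare treatment to the physician and keeps patients in follow-up after treatment changes. No exclusion matching the DR rule is stated.

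**The concern.** Exclusion can be set off by PASI above 5, the first component of the primary event. The second component is at least 3 months above that level. If a patient leaves the analysis at the start of that period, the flare cannot complete as an event there. The patients affected flare on a reduced dose and stay on it, which is part of how a dose-reduction strategy performs in practice.

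Per protocol is usually preferred in non-inferiority trials because non-adherence tends to shrink the difference under ITT. This deviation works the other way. Staying on a reduced dose through a flare would be expected to add persistent flares to the DR arm; ITT keeps them and the per protocol rule drops them. At stake is a non-inferiority claim from a main analysis that leaves out some DR failures, with no like rule for UC.

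**Working it through.** **1. Sequence of the rules for one DR patient on a lower dose**

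| Step | Section | Consequence |
|---|---|---|
| PASI above 5 at a visit | Dose reduction group | Patient should step back |
| Patient stays on the lower dose | Statistical analyses | Not included after the deviation |
| PASI still above 5 at least 3 months on | Definition of disease flare | Would be a primary event, but falls in excluded time |

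A persistent flare completed before the deviation, or occurring after a correct step-back, still counts.

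**2. The plan's own sample size, used for the arm sizes**

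The article gives 222 evaluable patients at 2:1, so 148 DR and 74 UC. It states no expected flare rate. With the unpooled formula, an equal rate of 17% in both arms gives UC n = (1.960 + 0.842)² × 0.17 × 0.83 × (1 + 1/2) / 0.15² = 73.8, rounded up to 74. DR is then 148 and the total 222. Adding 10% gives 244.2, matching the stated 244. The point does not depend on that rate.

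**3. Illustration at the margin**

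Assumptions, none of them from the article: UC rate 10%; true DR rate 25%, so the true excess is exactly 15 points; a share f of DR persistent flares falls in patients excluded at deviation. There are 148 × 0.25 = 37 DR events, so f = 10%, 20% or 30% means about 4, 7 or 11 patients.

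Observed DR rate:
- Kept in the denominator as event-free: 0.25(1 − f).
- Removed, event deviators only: 0.25(1 − f) / (1 − 0.25f).
- Removed, with k non-event deviators per event deviator: 0.25(1 − f) / (1 − 0.25f(1 + k)).

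The false non-inferiority rate comes from exact enumeration of the two binomials with the Farrington-Manning test at margin 0.15, one-sided 0.025, arm sizes 148 and 74. With f = 0 it is 2.7%.

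| f | Kept: rate, difference, false claim | Removed, k = 0 | Removed, k = 1 | Removed, k = 3 |
|---|---|---|---|---|
| 10% | 22.5%, 12.5 points, 8% | 23.1%, 13.1 points, 6% | 23.7%, 5% | 25.0%, 2.7% |
| 20% | 20.0%, 10.0 points, 20% | 21.1%, 11.1 points, 14% | 22.2%, 9% | 25.0%, 2.7% |
| 30% | 17.5%, 7.5 points, 40% | 18.9%, 8.9 points, 28% | 20.6%, 16% | 25.0%, 2.7% |

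Shrinking the DR arm by the patients removed lowers the removed figures slightly: at f = 30%, about 26% for k = 0 and 15% for k = 1.

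At k = 3, one deviator in four has a persistent flare. That 25% equals the arm's own risk, so removal no longer biases the difference; above three the bias would reverse.

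**4. Sensitivity to the assumptions**

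At UC 5% and DR 20%, the false-claim rates are 7.5%, 18% and 36% (kept) and 6%, 14% and 27% (removed, k = 0). With Wald limits at UC 10%, the rate starts at 2.0% and rises to 6%, 17% and 35% (kept) or 5%, 11% and 23% (removed, k = 0).

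**The case against.** **Size.** The article gives no rate of staying on the lower dose after a flare. It describes 3-monthly controlled visits with a required step-back, and expects persistent flares to be infrequent, so f could be small. At f = 5%, about 2 of 148 patients, the false-claim rate is 4–5%. The rule also removes deviators whose PASI would have settled, and those triggered by DLQI above 10 with PASI at or below 5. This stands: the k = 0 figures are a worst case for the removal convention, and a reader who infers bias toward non-inferiority under every convention goes too far.

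**Never counted.** A reader might infer that these flares can never be recorded. The documents do not support that. ITT includes deviators, and flares completed before deviation or after a correct step-back count in both analyses. Nor is the moment of deviation defined. If it were dated from a missed injection rather than the flare visit, some events could survive, given intervals of up to 24 weeks in Table 1. Hence the word generally.

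**ITT could not overturn the claim.** That is also not in the article. It calls ITT a sensitivity analysis and is silent on discordant results; such a rule may sit in a document not shown.

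**Conservatism.** ITT imputes by last observation carried forward, which can carry forward a pre-flare score. ITT is thus not shown to be the more conservative set overall. The narrower statement stands: for this deviation, per protocol is not conservative.

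**Safety.** The sentence putting all analysis on the per protocol set also reaches the adverse event comparison, where proportions and rate ratios "of SAEs and AEoSI will be described and differences between groups will be tested". But adverse events are recorded for 18 months and ITT covers all outcomes, so this is secondary.

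**Conclusion.** The point holds as limited here. The rule as written generally leaves out of the main analysis those DR flares during which the patient stays on the lower dose, with no stated counterpart in UC. The claim that per protocol is the most conservative analysis fails for this deviation.

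The bias is toward non-inferiority if deviators stay in the denominator as event-free, or if they are removed and their persistent-flare risk exceeds that of the rest of the DR arm. The article does not say which convention applies. Higher risk in patients already flaring on a reduced dose is plausible, but it is an assumption.

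The size cannot be derived from the article. In the illustration, with 10% to 30% of DR persistent flares affected, the false-claim rate moves from 2.7% to about 8–40% (kept) or at most about 6–28% (removed), with no bias in the removed case at three non-event deviators per event deviator. The planned ITT analysis will show these events, which limits the harm but does not correct the main result.

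**What to change.** Change the analysis wording in one or both of these ways:

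1. In the per protocol set, do not exclude or censor for failing to step back after a flare. Count PASI above 5 for at least 3 months by randomised arm, using the follow-up these patients complete anyway.
2. Make ITT co-primary, and claim non-inferiority only if the upper 95% limit is below 15% in both sets.

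For this deviation the first change brings the per protocol set close to ITT, so doing both is partly redundant. In either case, delete the statement that per protocol is the most conservative analysis. As a secondary change, compare SAEs and AEoSI in all randomised patients over full follow-up.

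The cost is slightly lower power where two analyses must succeed. No new data are needed, and no dosing rule changes.

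### The rule for patients lost to follow-up does not fit a crude 18-month proportion, and LOCF in the ITT analysis can bias the same comparison; under stated conditions both can favour non-inferiority

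*Protocol article*

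**What the plan says.** All references are to the Protocol article.

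- **Statistical analyses, primary (per protocol).** "Subjects lost to follow-up will be included in analyses until their lost to follow-up date only". The outcome is the proportion of patients with a persistent flare, with exact intervals per arm and a Fisher exact comparison. The denominator for patients lost early is not given. DR patients who should return to a higher dose but do not are cut off at the deviation.
- **Statistical analyses, time to event.** "Time until the first persistent flare in both groups will be graphically presented by Kaplan-Meier survival estimation". No estimate or interval is taken from these curves.
- **Statistical analyses, ITT (sensitivity).** "For the ITT analyses, last observation carried forward (LOCF) will be used for imputation of missing data". The ITT data are also said to be needed for the cost-effectiveness analysis. No other missing-data analysis is described.
- **Power and sample size analyses.** The margin is 15 percentage points, one-sided alpha is 0.025, power is 80% and allocation is 2:1. The plan states "we calculated that 222 patients need to be included to reject the null-hypothesis of inferiority", then allows for 10% drop-out to reach 244 (162 DR, 82 UC). No persistent-flare rate is stated.

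**The concern.** A two-by-two table records each patient as having had a persistent flare or not. It cannot take a patient as flare-free for four months and unknown afterwards. The stated rule therefore cannot be carried out with the stated estimator, and the analyst must choose between two departures from it. Dropping the patient contradicts the inclusion rule. Keeping the patient as flare-free assumes that no flare followed. Kaplan-Meier is the one planned method that honours the rule, and it is reserved for a graph.

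The ITT analysis makes the flare-free assumption explicitly for patients who leave clear. This sits badly with the article's Discussion, which justifies 18 months of follow-up by the need for more time to see the effect of DR with long-interval drugs. LOCF also errs the other way, because an open flare at the last visit is carried forward until it meets the three-month definition.

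The trial's central claim is at stake. In a non-inferiority comparison, events missed mainly in the arm with more events shrink the difference and make the claim easier.

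**Working it through.** **1. The plan's sample size.** No flare rate is given, so 222 can only be back-solved. With equal true rates p in both arms and unpooled variance, n(UC) = (1.960 + 0.842)² × p(1 − p) × (1 + 1/2) / 0.15². At p = 0.17 this is 7.849 × 0.1411 × 1.5 / 0.0225 = 73.8, so 74 UC + 148 DR = 222. A rate of 10% gives 144 and 20% gives 252; UC 5% against DR 10% gives 219. The flare rates below (UC 5%, 10%, 17%) are therefore assumptions. For drop-out, 222 × 1.1 = 244.2.

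**2. Attenuation if leavers count as flare-free.** Let d be the share lost and f the share of the 18-month flare risk that lies after departure. The observed rate is p × (1 − d × f). With d = 10% in both arms (the plan's figure, assumed equal by arm and unrelated to flares) and a true difference of 15 points:

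- losses spread evenly (f = 0.5): 15 × 0.95 = 14.25 points;
- all losses before any risk has accrued (f = 1): 15 × 0.90 = 13.5 points.

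**3. False non-inferiority rate at a true 15-point excess** (exact rejection probability of the Farrington-Manning test, one-sided 0.025). This test is an assumption, used to put a size on the effect.

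| Patients DR/UC | UC rate | No loss | f = 0.5 | f = 1 |
|---|---|---|---|---|
| 162/82 | 5% | 2.5% | 3.8% | 5.8% |
| 162/82 | 10% | 2.7% | 3.8% | 5.4% |
| 162/82 | 17% | 2.7% | 3.6% | 5.0% |
| 148/74 | 5% | 2.7% | 4.0% | 5.9% |
| 148/74 | 10% | 2.7% | 3.9% | 5.5% |
| 148/74 | 17% | 2.7% | 3.7% | 4.9% |

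The 162/82 rows match the reading that keeps leavers in the denominator.

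**4. Unequal loss** (UC rate 17%, DR rate 32%, normal approximation, 162/82).

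- DR 15%, UC 5%: 15 points shows as 13.0 (f = 0.5) or 11.1 (f = 1); false claims 5.5% or 11.1%.
- DR 5%, UC 15%: 15 points shows as 15.5 or 16.0; false claims 2.0% or 1.6%.

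The bias changes sign when d(UC) = d(DR) × p(DR)/p(UC). With 10% DR loss and a 15-point excess this is 0.10 × 0.20/0.05 = 40% for a UC rate of 5%, 0.10 × 0.25/0.10 = 25% for 10%, and 0.10 × 0.32/0.17 = 19% for 17%. With equal true rates and equal loss there is no bias.

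**5. Four estimators compared by simulation** (six three-monthly visits, 1,000,000 patients per arm). Assumed per visit: chance of a new flare 14% DR and 6% UC, chance that a flare continues 50%, base drop-out 1.75%. A persistent flare is two consecutive visits in flare. Differences in points:

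| Departure | True | Crude, leavers flare-free | LOCF | Completers only | Kaplan-Meier |
|---|---|---|---|---|---|
| Unrelated to flare, 10% per arm | 15.2 | 14.2 | 14.7 | 15.2 | 15.2 |
| 4 times as likely in flare, both arms | 15.1 | 13.3 | 15.3 | 14.2 | 14.6 |
| 4 times as likely in flare, DR only | 15.1 | 12.6 | 16.0 | 12.8 | 14.0 |

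The crude proportion and LOCF need not err in the same direction. Kaplan-Meier removes the bias only when loss is unrelated to flare.

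**The case against.** The strongest reply is that the per-protocol denominator is not stated, and an article may leave it to the full protocol. The inflation from 222 to 244 may even suggest that leavers are not meant to be evaluable. If they are excluded, loss unrelated to flare causes no bias. This stands as a limit on direction and size: the attenuation figures hold only if leavers stay in as flare-free. It does not remove the mismatch, because exclusion contradicts the rule that is written down.

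A reader might infer that both rules always pull the difference toward zero. The documents do not support that. The pull needs a true DR excess and UC losses not much above DR losses, and LOCF overstated the difference when departure followed flares.

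A reader might also infer that ITT is no check on the per-protocol result. That goes too far. Patients who deviate complete the study procedures and their data enter ITT, so ITT does restore observed outcomes that per protocol cuts off. It shares the weakness only for patients who leave clear.

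Flare-related drop-out in DR is possible in an open-label trial but is not shown. The plan has features that favour retention: unwilling patients may go back to the previous interval, patients stay in follow-up after treatment changes, and flares prompt extra visits. Finally, the Cost-effectiveness analysis section does not describe missing data, so the use of carried-forward costs and utilities there is inferred from the link to ITT. If they are used, the bootstrap would treat imputed values as observed. The size of that effect was not calculated.

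**Conclusion.** The point holds in conditional form. The loss-to-follow-up rule cannot be applied to a crude 18-month proportion, and LOCF is a poor imputation for an endpoint defined by duration. With 10% loss in each arm, unrelated to flare, and leavers counted as flare-free, the crude difference shrinks by 0.75 to 1.5 points against a margin of 15; in the simulation LOCF shrank it by 0.5. The false non-inferiority rate on the crude proportion then rises from about 2.5-2.7% to 3.6-5.9%. The upper end needs every loss to occur before any flare risk has accrued. The effect is larger if DR loses more patients than UC, nil for completers only when loss is unrelated to flare, and reversed with sufficiently higher UC losses or, under LOCF, with flare-related departure. All flare rates and loss patterns are assumptions, since the article gives only the overall 10%. This should be corrected before analysis, but it does not by itself undermine the trial.

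**What to change.** 1. **Per protocol.** Estimate the 18-month risk of a persistent flare in each arm by Kaplan-Meier, censoring at loss. Base the non-inferiority decision on the confidence interval for the difference of the two risks (Greenwood or bootstrap). This carries out the rule already written.
2. **ITT and cost-effectiveness.** Replace LOCF by multiple imputation, by arm, of visit-level PASI, utilities and costs, using baseline values, biologic and earlier visits. Derive persistent flare from the imputed visits.
3. **Sensitivity to informative loss.** Censoring assumes that loss is unrelated to flare, so vary the flare risk among losses in both arms. Counting all DR losses and no UC losses as flares is the extreme case: with 10% loss and none of the 16 lost DR patients already counted, it adds up to 16/162 = 9.9 points, so it should be read as a bound.

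The three-monthly visit data are already collected. The cost is programming and a possibly slightly wider interval.

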**Table 2 Tab2:**
[figure not shown]
Schedule of enrolment, interventions, and assessments by study time point

*Abbreviations*: *M* months, *PASI* Psoriasis Area and Severity Index, *DLQI* Dermatology Life Quality Index, *EQ-5D-5L* European Quality of Life-5 Dimensions-5 Level questionnaire, *SF-36* Short Form-36 questionnaire, *iMTA MCQ* institute for Medical Technology Assessment Medical Consumption Questionnaire, *PCQ* Productivity Cost Questionnaire

Our primary outcome is non-inferiority of the incidence proportion of persistent flares (PASI > 5 for ≥ 3 months) in the intervention group. If the 95% confidence interval from the difference in incidence of persistent flares in the intervention group versus control group exceeds the non-inferiority margin (15% difference in persistent flares) at 18 months of follow-up, it can be concluded that non-inferiority could not be demonstrated for DR.

Our secondary study outcomes are as follows:

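### The methods and rule in Statistical analyses do not deliver the upper confidence limit of the difference that the article's own non-inferiority criterion requires

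*Protocol article*

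**What the plan says.** All references are to the protocol article.

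- **Procedures and outcome measures** (text below Table 2) defines the primary outcome: "Our primary outcome is non-inferiority of the incidence proportion of persistent flares". It bases the conclusion on an interval for the difference: "If the 95% confidence interval from the difference in incidence of persistent flares in the intervention group versus control group exceeds the non-inferiority margin" of 15%.
- **Power and sample size analyses** makes this precise. Non-inferiority is not demonstrated "If the upper limit of the 95% confidence interval of the difference in persistent flares between the intervention group versus control group exceeds 15" per cent at 18 months. The section adds that "the margin refers to the upper limit of the 95% confidence interval of the difference in persistent flares which should not exceed 15" per cent, and that the point estimate should therefore lie well below the margin. It uses a one-sided alpha of 0.025, 80% power and 2:1 allocation, giving 222 evaluable patients (244 with drop-out).
- **Statistical analyses** gives the methods for the primary outcome: "Confidence intervals of proportions will be calculated by Fishers exact tests (Clopper-Pearson), and the proportions will be compared using Fisher exact tests", with a named software calculator. The rule follows in a different form: "If the difference in incidence proportion of persistent flares in the intervention group versus the UC group exceeds the non-inferiority margin" at 18 months, non-inferiority was not demonstrated. No confidence limit is mentioned.

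No section names a method for an interval of the difference, or a test whose null is a 15-point excess.

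**The concern.** The section that says how the primary outcome will be analysed does not match the criterion that the analysis must serve, in two ways.

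**Method.** Clopper-Pearson is a one-sample interval, and two of them do not combine into an interval for a difference. Fisher's exact test asks whether the two flare proportions are equal. The trial's null hypothesis is that DR is worse by 15 points or more. A p-value for equality has no defined error rate against that null.

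**Rule.** The Statistical analyses section compares the difference with 15%. The sample size section compares the upper limit of its interval with 15% and says explicitly why the two are not the same.

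An analyst working from the analysis section alone would hold a point difference, two per-arm intervals and a p-value for equality. None of these is the quantity that decides the trial. The interval formula would then have to be chosen later, in an open-label trial, and formulas can differ by enough to matter when the result lies near the margin.

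**Working it through.** **Inputs.** From Power and sample size analyses: margin 15 points, one-sided alpha 0.025, power 0.80, 2:1 allocation, 222 evaluable patients, hence 222 × 2/3 = 148 DR and 222 × 1/3 = 74 UC. The article gives no numerical flare rates, so the UC rate is an assumption, varied from 2% to 17%.

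**The plan's figure.** The 222 cannot be derived uniquely without flare rates, but it can be reached. With 17% in both arms and the unpooled normal formula:

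n(UC) = (1.960 + 0.842)² × (0.17 × 0.83/2 + 0.17 × 0.83) / 0.15² = 73.8, rounded up to 74, and 74 × 3 = 222.

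Other pairs (for example UC 9%, DR 12%) also give 222. The number therefore fits a test against the 15-point margin, which is the criterion in the sample size section.

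**Step 1: the named methods and the criterion on example data.** With p₁ the DR proportion, p₂ the UC proportion and d = p₁ − p₂:

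- Wald upper limit = d + 1.96 × √(p₁(1−p₁)/148 + p₂(1−p₂)/74)
- Newcombe upper limit = d + √((u₁−p₁)² + (p₂−l₂)²), where u₁ and l₂ are Wilson limits

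For DR 30/148 (20.3%) and UC 10/74 (13.5%), d = 0.0676:

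- Wald: 0.0676 + 1.96 × √(0.001092 + 0.001579) = 0.169.
- Newcombe: u₁ = 0.2746 and l₂ = 0.0751, so 0.0676 + √(0.0719² + 0.0600²) = 0.161.

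| DR | UC | Difference | Fisher p | Newcombe upper | Wald upper | Criterion in sample size section |
|---|---|---|---|---|---|---|
| 30/148 | 10/74 | 6.8 | 0.27 | 16.1 | 16.9 | not shown |
| 37/148 | 10/74 | 11.5 | 0.056 | 21.1 | 21.9 | not shown |
| 14/148 | 1/74 | 8.1 | 0.023 | 14.0 | 13.5 | shown |
| 15/148 | 1/74 | 8.8 | 0.024 | 14.8 | 14.3 | shown |

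In the first two rows Fisher is non-significant and the point difference is below 15, yet non-inferiority is not shown. In the last two Fisher is significant, yet non-inferiority is shown. In the last row the Miettinen-Nurminen limit is 14.98, so reasonable formulas run from 14.3 to almost 15.0.

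**Step 2: the per-arm intervals do not substitute.** For 14/148 and 1/74 the Clopper-Pearson intervals are 5.3–15.4% and 0.03–7.3%. Subtracting the extremes gives 15.36 − 0.03 = 15.3 points, above the margin, whereas the interval for the difference ends at 14.0 (Newcombe). Ad hoc use of the per-arm intervals would reverse the conclusion.

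**Step 3: error at a true excess of exactly 15 points.** This is an exact sum of binomial probabilities over all outcomes with 148 and 74 patients.

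| Assumed UC rate | Newcombe upper limit ≤ 15 | Wald upper limit ≤ 15 | Point difference ≤ 15 | Fisher p ≥ 0.05 |
|---|---|---|---|---|
| 2% | 2.8% | 2.6% | 52% | 3.5% |
| 5% | 2.8% | 2.3% | 52% | 10.8% |
| 10% | 2.8% | 2.0% | 51% | 22.6% |
| 17% | 3.0% | 2.0% | 51% | 34.7% |

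A limit for the difference stays near the planned 2.5%. The literal rule in Statistical analyses does not. The Fisher column is an error rate only if non-significance is taken as non-inferiority.

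**Step 4: power after the fix.** With 17% in both arms, the upper-limit rule has power 82% (Wald) or 86% (Newcombe), so 222 evaluable patients remain enough under that assumption.

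**The case against.** The strongest defence is that the article states the right criterion twice, with its one-sided alpha and the null of inferiority. Read as a whole, it requires an interval for the difference. Only the formula is unnamed, and a condensed article may leave that to a full protocol or SAP. The Clopper-Pearson and Fisher sentence could be description plus a supplementary comparison, and the rule that follows could be shorthand.

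Much of this stands. A reader might infer that the plan as a whole cannot produce the interval it needs, or that a non-significant Fisher test is its non-inferiority rule. The documents support neither reading. The outcome and sample size sections call for the interval, and no section equates a Fisher result with non-inferiority. The Fisher percentages therefore measure a possible misreading, and they are small if UC flares are rare (3.5% at 2%). That matters because the article itself expects persistent flares to be infrequent. Nor is a significant Fisher test beside a met criterion a contradiction: a difference can exceed zero and still lie within the margin.

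What does not stand is the claim of mere omission. The section names methods, and even software, for the primary outcome. Those methods do not yield the deciding quantity, and its wording of the rule differs in substance from the sample size section.

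**Conclusion.** The concern holds as an internal mismatch: the criterion is right in the outcome and sample size sections, while the named methods and the restated rule in Statistical analyses do not implement it. Applied literally, the restated rule would accept non-inferiority in 51–52% of trials at a true 15-point excess, against 2.8–3.0% for a Newcombe upper limit. Misreading Fisher would mislead in 3.5% to 35%.

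These figures rest on 148 and 74 evaluable patients and assumed UC rates of 2–17%. They show the consequence of following the wrong passage. They are not the error rate of the trial if the sample size section governs. The mismatch concerns the primary conclusion, so it should be settled before outcomes are compared between arms.

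**What to change.** In Statistical analyses, state the primary analysis as the risk difference in persistent flares at 18 months (DR minus UC) with one prespecified two-sided 95% interval, for example Miettinen-Nurminen (score). Conclude non-inferiority only if its upper limit does not exceed 15%, in the same terms as the sample size section. Name a single formula: Newcombe is also acceptable, but it is not the same procedure as a score test against the margin, so the two should not be offered as equivalent. Keep Clopper-Pearson for describing each arm, and label the Fisher test supplementary or drop it.

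The cost is one or two sentences and standard software. Margin, criterion, sample size and data collection are unchanged.
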